#### Secondary outcomes

2.6.2

(1)Quality of life will be assessed by a validated patient-reported outcome scale,^[18]^ which includes 27 items and assesses the impacts of hypertension on the 3 dimensions of quality of life, namely, the physical dimension (18 items), psychological dimension (4 items), and family-social dimension (5 items). Each item is divided into 5 categories, with each category receiving 0 to 4 points in sequence. A higher score indicates a worse quality of life. The total score equals the sum of the score of each item, ranging from 0 to 108 points. The detailed content of the scale is provided in the Supplemental Content (http://links.lww.com/MD/E870). We will also analyze the scores of individual dimensions separately.(2)Indicators related to diabetes mellitus, including changes in fasting blood glucose (mg/dl) and hemoglobin A1c (%), will be assessed.(3)Indicators related to dyslipidemia, including changes in total cholesterol (mg/dl), triglycerides (mg/dl), low-density lipoprotein cholesterol (mg/dl), and high-density lipoprotein cholesterol (mg/dl) levels, will be assessed.(4)Indicators related to hypertensive renal disease, including urinary albumin (g/l) and serum creatinine (μmol/l) levels, will be assessed.(5)Patient compliance will be determined. Patient compliance will be deemed poor if a patient administers heat-sensitive moxibustion fewer than 8 times per month. The proportion of patients with poor compliance will be assessed.

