### Statistical analysis plan

2.12

The analyses of the primary outcomes will be performed in the intention-to-treat population where either patients in the control group who performed heat-sensitive moxibustion or patients in the heat-sensitive moxibustion group who stopped moxibustion during follow-up will still be kept in their original group. Meanwhile, we will also perform sensitivity analyses using the perprotocol population to test the robustness of the main analysis. All analyses of the secondary outcomes will be performed in the per-protocol population. We will decide whether to impute missing data and which method should be used to impute missing data based on the actual distribution of the missing data.

For categorical or ordinal variables, we will calculate frequencies and percentages as the descriptive statistics and compare the between-group differences using the chi-square test or the linear-by-linear association test. We will present the means with standard deviations/errors and medians with interquartile ranges for continuous variables with normal and skewed distributions, respectively; the independent *t* test or the Mann-Whitney *U* test will be used to compare 2 groups. The effects of heat-sensitive moxibustion on the outcomes will be inferred using analysis of covariance or a logistic regression model adjusted for age, course of hypertension, baseline SBP, comorbidities, education level, smoking status, drinking status, and types of antihypertensive drugs recoded as dummies. The effects will be measured as the mean difference or odds ratio with a 95% confidence interval, and *P*-values will also be calculated. In addition, we will test 2 subgroup hypotheses:

(1)the dose of moxibustion: ≥3 sessions/wk vs <3 sessions/wk;(2)whether the heat-sensitive sensation appears: yes vs no.

The significance level indicating a difference between groups and subgroups will be α = 0.05. We will use R version 4.0.2 (The R Foundation for Statistical Computing, Austria) to run all statistical analyses.

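### The adjusted analysis of urinary albumin and triglycerides is fixed as a mean difference without the variable's own baseline; if albumin is strongly skewed, a log-scale ANCOVA would be clearly more precise

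*Protocol article*

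**What the plan says.** Section 2.12 (Statistical analysis plan) treats skew in two places. Descriptive statistics are to be means or "medians with interquartile ranges for continuous variables with normal and skewed distributions, respectively", and the unadjusted comparison of the groups is a t test or a Mann-Whitney test.

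For the treatment effect the section says: "The effects of heat-sensitive moxibustion on the outcomes will be inferred using analysis of covariance or a logistic regression model". The covariates are age, duration of hypertension, baseline systolic pressure, comorbidities, education, smoking, drinking and drug types. The effect measure follows: "The effects will be measured as the mean difference or odds ratio with a 95% confidence interval". No transformation, ratio measure or adjusted rank method is named, and the baseline value of a laboratory outcome is not among the covariates.

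Section 2.6.2 (Secondary outcomes) gives the laboratory outcomes in original units. Triglycerides are a change in mg/dl. The renal outcomes are levels, "including urinary albumin (g/l) and serum creatinine (μmol/l) levels, will be assessed".

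**The concern.** The allowance for skew stops at the unadjusted comparison. Under section 2.4 patients enter the group they prefer, and the Discussion names the nonrandomized design as the main limitation. The adjusted estimate is therefore the one a reader must rely on, and for a skewed laboratory variable it is a difference of arithmetic means.

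If the variable has a long right tail, a few high values carry much of the variance and the confidence interval widens. Leaving out the variable's own baseline widens it further, because that baseline is usually the strongest predictor of the follow-up value. What is at stake is the precision and stability of two secondary laboratory results.

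**Working it through.** **Figure to reproduce.** There is none: the article states no power, standard deviation or target effect for any laboratory outcome.

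**Inputs from the article.** Section 2.11 plans 300 per group with 20% attrition, so n = 300 × 0.8 = 240 per group. Section 2.12 sets α = 0.05, taken here as two-sided.

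**Assumptions, not in the article.** Values are lognormal with log-scale SD s, and baseline and follow-up have log-scale correlation ρ = 0.7. R is the ratio of geometric means. Strong skew, as might hold for albumin, is s = 1.0 to 1.3 with R = 0.8. Mild skew, as might hold for triglycerides, is s = 0.5 with R = 0.9. No confounding and no other covariates are simulated.

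**Log-scale ANCOVA with log baseline, by formula.** z = |ln R| / [s·√(1−ρ²)·√(2/n)], and power = Φ(z − 1.96). Here √(1−0.49) × √(2/240) = 0.714 × 0.0913 = 0.0652.
- s = 1.0: 0.2231/0.0652 = 3.42, Φ(1.46) = 93%.
- s = 1.3: 0.2231/0.0848 = 2.63, Φ(0.67) = 75%.
- s = 0.5: 0.1054/0.0326 = 3.23, Φ(1.27) = 90%.

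**Difference of mean levels without own baseline, by formula.** z = (1−R) / [CV·√((1+R²)/n)], with CV = √(exp(s²)−1).
- s = 1.0: CV = 1.311, z = 0.2/(1.311 × 0.0827) = 1.85, Φ(−0.11) = 46%.
- s = 1.3: CV = 2.102, z = 0.2/(2.102 × 0.0827) = 1.15, Φ(−0.81) = 21%.
- s = 0.5: CV = 0.533, z = 0.1/(0.533 × 0.0868) = 2.16, Φ(0.20) = 58%.

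**Simulated power for all three models.**

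| Setting | Raw, no own baseline | Raw ANCOVA, own baseline | Log ANCOVA, log baseline |
|---|---|---|---|
| s = 1.0, R = 0.8 | 49% | 66% | 93% |
| s = 1.3, R = 0.8 | 23% | 32% | 76% |
| s = 0.5, R = 0.9 | 59% (level) to 74% (change) | 84% | 91% |

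The first and last columns agree with the formulas to within about 3 points. A separate run of 3,000 trials per setting gave 65 vs 92%, 34 vs 75% and 83 vs 89% for the last two columns, with type I error between 4.4% and 5.7%.

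**Splitting the loss.**
- At s = 1.0, the scale accounts for 93 − 66 = 27 points and the missing baseline for 66 − 49 = 17.
- At s = 1.3, the scale accounts for 76 − 32 = 44 points and the missing baseline for 32 − 23 = 9.
- At s = 0.5 with triglycerides analysed as a change, the scale accounts for 91 − 84 = 7 points (89 − 83 = 6 in the separate run) and the missing baseline for 84 − 74 = 10.

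**Sensitivity to the assumed skew.** With ρ = 0.6 and the effect set to give 80% power on the log scale, raw ANCOVA with own baseline has simulated power of 77, 74, 67, 53, 40 and 32% at s = 0.3, 0.5, 0.7, 1.0, 1.3 and 1.5. The highest 2% of patients contribute 29% of the total sum of squares at s = 0.5 and 55% at s = 1.0.

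**The case against.** The strongest objection is that this is a condensed article. Transformations are ordinary detail for a full analysis plan that is not shown, and section 2.12 never says that values stay untransformed. This stands in part: the original scale is inferred from the effect measure and the units. But the section is not silent. It names the model and the effect measure for the outcomes, and a ratio of geometric means is neither of the two measures named. The point is that a better method exists than the one stated, not that a detail is absent.

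The second objection is that the size rests on assumed distributions. That stands fully. Section 2.3 also excludes hypertension secondary to kidney disease and serum creatinine above twice the upper limit of normal, which may shorten the albumin tail. Secondary outcomes use the per-protocol set, so 240 per group is itself approximate.

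A reader might infer more than the article supports:
- **That much power is lost for triglycerides too.** At mild skew the scale costs only a few points, and the own baseline matters more.
- **That the adjusted and the Mann-Whitney results will contradict each other.** No rate of disagreement has been calculated. In self-selected groups an unadjusted and an adjusted result may differ through confounding alone, which a log transformation does not cure.
- **That the planned test is invalid.** Simulated type I error stays near 5% in these settings, and a difference of arithmetic means is a legitimate estimand.
- **That special rules for undetectable values, or robust standard errors for the other outcomes, are needed.** The article gives no detection limit or censoring share, and no calculation here supports either.

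**Conclusion.** The concern holds as a low-priority improvement. The section foresees skew but carries no provision for it into the one analysis that addresses confounding, and it omits the laboratory variable's own baseline. For urinary albumin the loss of precision is substantial if the log-SD is about 1.0 or more: roughly 27 to 44 points of power from the scale alone at log-SD 1.0 to 1.3 for a 20% lower geometric mean. For triglycerides at an assumed log-SD of 0.5, the scale costs about 6 to 7 points for a 10% reduction. These figures depend on the lognormal shape, the correlation of 0.7 and 240 analysed per group. The effect is on precision and interpretability in secondary outcomes. Neither type I error nor the blood-pressure and drug-dose conclusions are touched.

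**What to change.** In section 2.12, state that urinary albumin and triglycerides will be analysed by ANCOVA on the log scale, with the log baseline of the same variable added to the listed covariates, and that the effect will be reported as a ratio of geometric means with 95% CI.

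The cost is one sentence, and an effect expressed as a ratio instead of a difference in g/l or mg/dl. One point to confirm: the text of section 2.8 names blood and urine indicators at months 6 and 12 but not among the month 0 items. The visit schedule is in a figure not available here, and the change outcomes imply a baseline sample. The authors should check that urinary albumin, which is defined as a level, is also measured at month 0.

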### Site and participant recruitment

2.2

We will recruit patients with primary hypertension from 4 communities: the Nangang community, the Honggutan community, the Shengmi community in Nanchang city, and the Gaofu town community in Fu Zhou city. Recruitment will occur through community doctors’ oral communication with individuals, posters, and mobile advertising. Patients who express a preliminary willingness to participate in the study will be screened for eligibility and informed about the entire study process, benefits, and potential harms. Eligible patients will formally enter the study cohort after signing the informed consent form. The overall study design is shown in Figure 1.

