### Training and assignment

2.4

There is a community health service center in each community. Before the study begins, we will invite senior experts to give 4 lectures (once per week) for residents in each community health service center to introduce the principal and anticipated efficacy of the use of heat-sensitive moxibustion for the management of hypertension. After fully comprehending the relevant knowledge, eligible patients will enter the heat-sensitive moxibustion group or the control group according to their preferences. Investigators and community doctors will not provide any advice regarding the group selection. For patients entering the heat-sensitive moxibustion group, community doctors will further provide one-on-one training, explaining how to perform heat-sensitive moxibustion, how to identify heat-sensitive acupoints, and how to avoid burns, among other safety precautions.

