### Study visits

2.8

During the 1-year follow-up period, the investigators will visit the patients monthly at the community health service centers, which are generally within 1 km of the patients’ homes. At month 0 (baseline visit), we will collect demographic characteristics (name, phone number, sex, age, education level, height, and weight) and disease-related characteristics (SBP, DBP, course of hypertension, comorbidities, smoking, drinking, and type and dosage of antihypertensive drugs currently used). At months 6 and 12, we will measure blood pressure, changes in doses of antihypertensive drugs, quality of life, blood and urine indicators, and AEs. The other regular visits (ie, months 1–5 and 7–11) will involve the distribution of moxa rolls and moxibustion boxes to patients, the assessment of patient compliance and the adjustment of the doses of antihypertensive drugs. A detailed schedule of the study visits is shown in Figure 2.

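### The single adjustment list omits community, sex and BMI, and adjusts DBP change and drug-dose change for baseline SBP but not for their own recorded month-0 values

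*Protocol article*

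**What the plan says.** Allocation (section 2.4): "eligible patients will enter the heat-sensitive moxibustion group or the control group according to their preferences".

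Model (section 2.12): "The effects of heat-sensitive moxibustion on the outcomes will be inferred using analysis of covariance or a logistic regression model". The covariates are then named in the same sentence, so that each model is "adjusted for age, course of hypertension, baseline SBP, comorbidities, education level, smoking status, drinking status, and types of antihypertensive drugs recoded as dummies". One list serves all outcomes, and nothing in the wording marks it as a set of examples. No matching, propensity or site-stratified analysis is described.

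Data held at month 0 (section 2.8): the personal items are given as "demographic characteristics (name, phone number, sex, age, education level, height, and weight". The clinical items form a second group, given as "disease-related characteristics (SBP, DBP, course of hypertension, comorbidities, smoking, drinking, and type and dosage of antihypertensive drugs currently used".

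Sites (section 2.2): "We will recruit patients with primary hypertension from 4 communities", in two cities.

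Primary outcomes (section 2.6.1): changes in SBP and DBP, and percentage change in antihypertensive dose.

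Sample size (section 2.11): sized on a 5 mm Hg change in SBP with SD 20 mm Hg. The number was then raised to 300 per group, with adjustment for more confounders as the reason. The Discussion concedes bias from unknown confounders only.

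**The concern.** When patients select their treatment, the covariate list carries the causal claim. A variable that is known, recorded and plausibly related to both choice and outcome should be in the model unless there is a reason to leave it out. None is given here.

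**Community.** Each community has its own health centre and its own lecture series. Community doctors give the one-on-one training, collect the data and decide on drug-dose adjustment, which is itself a primary outcome. Uptake and outcome may both vary by community. If they do, the unadjusted community difference enters the treatment estimate.

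**Own baseline.** DBP change and dose change are modelled with baseline SBP only. If the groups differ in baseline DBP beyond what SBP explains, regression to the mean in DBP will look like a treatment effect.

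**Sex and BMI.** Sex, height and weight are collected but not used for adjustment.

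Enlarging the sample does not remove any of these biases.

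**Working it through.** **1. Covariate list against recorded data**

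| Variable | Recorded at or before month 0 | In the model |
|---|---|---|
| Baseline SBP | yes (2.8) | yes |
| Baseline DBP | yes (2.8) | no |
| Drug types | yes (2.8) | yes |
| Drug dosage | yes (2.8) | no |
| Sex | yes (2.8) | no |
| Height and weight, hence BMI | yes (2.8) | no |
| Community | known at recruitment (2.2) | no |
| Quality of life, blood and urine indicators | not stated in the text | no |

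On the last row, the text of 2.8 says "At months 6 and 12, we will measure blood pressure, changes in doses of antihypertensive drugs, quality of life, blood and urine indicators, and AEs". Section 2.6.2 words the diabetes indicators as "changes in fasting blood glucose (mg/dl) and hemoglobin A1c (%), will be assessed", and the lipids likewise, which implies a baseline. The visit schedule in Figure 2 is not available to settle it.

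**2. Is baseline SBP an adequate stand-in for baseline DBP?** Section 2.3 admits patients with SBP of at least 130 or DBP of at least 90 mm Hg. A patient can therefore enter on DBP alone, so SBP is an incomplete proxy.

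**3. Illustration for community (all inputs assumed).** Take four equal communities with uptake p and mean SBP change m, centred at zero.

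Bias = Σ(p·m)/Σp − Σ((1−p)·m)/Σ(1−p). In each case below Σp = Σ(1−p) = 2.

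- Uptake 35, 45, 55, 65%; 2 mm Hg per step (m = −3, −1, 1, 3): Σ(p·m) = −1.05 − 0.45 + 0.55 + 1.95 = 1.0. Bias = 0.5 − (−0.5) = 1.0 mm Hg, 20% of 5.
- Uptake 30, 40, 60, 70%; 2 mm Hg per step: Σ(p·m) = −0.9 − 0.4 + 0.6 + 2.1 = 1.4. Bias = 1.4 mm Hg, 28% of 5.
- Uptake 45, 48, 52, 55%; 2 mm Hg per step: Σ(p·m) = −1.35 − 0.48 + 0.52 + 1.65 = 0.34. Bias = 0.34 mm Hg, 7% of 5.
- Uptake 35, 45, 55, 65%; 0.5 mm Hg per step: one quarter of the first case, 0.25 mm Hg, 5% of 5.

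The bias is zero if uptake, or mean change, is the same in all communities. The sign is unknown.

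**4. Illustration for DBP (all inputs assumed).** DBP has SD 10 mm Hg, SBP–DBP correlation 0.6 and retest correlation 0.6. There is no true effect, and patients with higher DBP are more likely to choose moxibustion, with log-odds g per SD. Simulated bias in the DBP-change difference, with 600 patients and 2,000 repeats:

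| g | Adjusted for SBP only | Baseline DBP added |
|---|---|---|
| 0.2 | −0.50 | 0.00 |
| 0.4 | −0.99 | 0.01 |
| 0.8 | −1.87 | 0.02 |

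Rough check at g = 0.2: the imbalance not explained by SBP is about 0.2 × (1 − 0.6²) = 0.128 SD, or 1.28 mm Hg. Times −(1 − 0.6) = −0.4, this gives −0.51 mm Hg.

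**5. Cost in precision.** Added terms: 3 (community) + 1 (sex) + 1 (BMI) + 1 (own baseline) = 6. For SBP change it is 5, because its baseline is already in. Evaluable patients: 600 × 0.8 = 480. With an assumed 20 existing parameters, and a standard error taken as proportional to √(1/(N − k − 2)), the ratio is √(458/452) = 1.007. That is about 0.7%, before any gain from explained variance.

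**The case against.** Several points on the other side are sound.

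- SBP change is a primary outcome and the one used for sizing, and baseline SBP is in the model. A reader might infer that no outcome is adjusted for its own baseline. For SBP that is wrong.
- A reader might also infer that every missing baseline value is on file at month 0. The text does not show this for quality of life or the laboratory outcomes, and with Figure 2 unavailable its silence is not evidence of a defect. Quality of life, urinary albumin and creatinine are not worded as change scores either, so the regression-to-the-mean argument is not established for them.
- Community is a plausible confounder, not a demonstrated one. Every centre receives the same number of lectures, staff give no advice on group choice, blood pressure is the mean of three electronic readings, and investigators are trained in standard procedures. These steps reduce community differences but do not exclude them.
- A step of 2 mm Hg means a 6 mm Hg spread between the extreme communities, more than the target effect, and assumes that the listed covariates explain none of it. The low cases in the working are as tenable as the high ones.
- Percentage change in dose is already scaled to the starting dose. That does not make it independent of the starting dose, but no size for the dependence can be given.

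A separate analysis plan might hold a fuller list. The article, however, states a closed list under its own analysis-plan heading, so this is a stated choice rather than detail left out.

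**Conclusion.** The point holds for community, sex and BMI in every model, and for the own baseline of DBP change and drug-dose change. It does not hold for the own baseline of SBP change. For secondary outcomes it applies only where a month-0 value exists.

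The size is not derivable from the document. On assumed inputs, omitting community moves the SBP difference by about 0.25 to 1.4 mm Hg (5% to 28% of the target), and by nothing if communities do not differ in uptake or in outcome. If baseline DBP drives group choice as assumed, adjusting DBP change for baseline SBP alone leaves about −0.5 to −1.9 mm Hg. No figure is offered for sex, BMI or dosage.

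This should be fixed: the variables are recorded, the design depends on adjustment, and the cost is small. The evidence does not show that the SBP result would be materially wrong without the change.

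**What to change.** In section 2.12, before outcome data are seen:

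1. Add community (4 levels), sex and BMI to every outcome model, keeping the covariates already listed.
2. Add baseline DBP to the model for DBP change.
3. Add baseline drug dosage to the model for the dose outcome. Section 2.5 leaves drug type and dose unrestricted, so the sponsor must state how dosage across different drugs is put on one scale for analysis.
4. For each secondary outcome with a month-0 value, add that value. This does not apply to compliance, which has no baseline.
5. Check against Figure 2 whether quality of life and laboratory values are taken at month 0 in both groups, and make the text of section 2.8 say so if they are.

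Items 1 and 2 need no new data and only a change of wording. Item 3 needs no new data but does need the dosage scale defined. Item 4 would touch data collection only if the month-0 values turn out not to be planned. The statistical cost is the roughly 6 degrees of freedom shown in the working.

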### Interventions and co-interventions

2.5

Patients in the heat-sensitive moxibustion group will self-administer heat-sensitive moxibustion for one year while maintaining their original antihypertensive drugs. With the doctors’ help, the patients will first identify the heat-sensitive acupuncture points near CV8 (Shenque, the center of the navel), CV4 (Guanyuan, approximately 10 cm below the navel), and bilateral ST36 (Zusanli, approximately 7 cm below the lateral of the knee) and then perform moxibustion on the heat-sensitive acupoints. Self-sticking mini-moxa rolls will be used as the combustible material, which can be placed and burned in a moxibustion box (Fig. 2). A matching velvet bag can be used to wrap the moxibustion box to avoid burns. The suggested dose of moxibustion will be one moxa roll (approximately 30 minutes) per session, with 1 session per day and 7 sessions per week. Driven by a pragmatic design, we will allow the patients to adjust the dose of moxibustion to make it convenient, but they need to truthfully report the adjusted dose. Patients in the control group will only maintain their original antihypertensive drugs and will not perform heat-sensitive moxibustion. There will be no restriction on the type and dose of antihypertensive drugs, but other acupoint stimulation therapies, such as acupuncture, will be prohibited.

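### The two subgroup hypotheses are defined only in the moxibustion arm and arise after group choice, so they cannot test effect modification and support no causal dose-response conclusion

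*Protocol article*

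**What the plan says.** In section 2.12 (Statistical analysis plan), after describing the adjusted group comparison, the protocol article states: "In addition, we will test 2 subgroup hypotheses". The first is "the dose of moxibustion: ≥3 sessions/wk vs <3 sessions/wk". The second is "whether the heat-sensitive sensation appears: yes vs no". On error control it says: "The significance level indicating a difference between groups and subgroups will be α = 0.05". Neither analysis is called exploratory or descriptive.

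Section 2.5 (Interventions and co-interventions) bears on both variables. On dose: "we will allow the patients to adjust the dose of moxibustion to make it convenient, but they need to truthfully report the adjusted dose". Controls, it says, "will only maintain their original antihypertensive drugs and will not perform heat-sensitive moxibustion". The same section has patients in the moxibustion group locate their heat-sensitive points with a doctor's help before they start treating themselves. The Introduction describes the sensation as something felt when moxibustion is applied to such points.

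**The concern.** A subgroup hypothesis normally asks whether the treatment effect differs between kinds of patient. That needs a characteristic which can be observed in both groups and which treatment does not shape. Neither variable here qualifies. Sessions per week is a record of how the patient used the intervention, and sensation is an experience that the intervention produces.

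A significant difference would be easy to read as evidence that more moxibustion lowers blood pressure further, or that the heat-sensitive principle itself works. Adherence behaviour and feedback between blood pressure, drug changes and continued use could produce such a difference with no treatment effect. The stakes follow from the article's own aims: the Introduction presents heat-sensitive points as the therapy's main innovation, and the Discussion expects the findings to bear on partial replacement of drugs and on public health policy.

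**Working it through.** The protocol gives no figure for the subgroup tests, so there is none to reproduce. The check has two parts.

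**Structure**

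- *Value in controls.* By section 2.5 controls do not use moxibustion. Section 2.12 foresees that some may cross over and keeps them in their original group, but a few self-selected crossovers do not make a control stratum. No interaction term can be estimated.
- *Timing of dose.* Dose is adjusted by the patient during the year. It is not in the month 0 data listed in section 2.8.
- *Timing of sensation.* It is not in the month 0 list either, and section 2.12 does not say when it is classified. Point-finding is described only for patients already in the moxibustion group (sections 2.4 and 2.5). Even at its earliest, sensation follows group choice and exists in one arm only.
- *Who falls in the lower dose stratum.* Patients who stop moxibustion stay in their group (section 2.12). If classified by the dose they actually used, they would tend to land below 3 sessions per week, so that stratum partly reflects discontinuation.
- *Feedback.* At each regular visit doctors may change drug doses according to the last month's blood pressure (section 2.6.1). Blood pressure, drug dose and continued use can therefore influence one another.
- *Adjustment.* The model covariates are age, course of hypertension, baseline SBP, comorbidities, education, smoking, drinking and drug types, all collected at month 0 (section 2.8). They cannot remove reasons for dose change that arise later.
- *Each stratum against all controls.* This sets a self-selected part of one arm against an unselected arm and is confounded for the same reasons.

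**Size, as an illustration with no true effect**

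Inputs from section 2.11: SD of SBP change 20 mm Hg, 300 per group, 20% attrition. Completers in the moxibustion arm: 300 × 0.8 = 240. Assumptions: normally distributed dose, a split into halves of 120, a correlation r between chosen dose and SBP change that is wholly non-causal, and no covariate adjustment.

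- Difference between halves = 2 × 0.798 × r × 20, where 0.798 is the mean of a standard normal variable above its median.
- Standard error = 20 × √(2/120) = 2.58 mm Hg.
- Chance of significance ≈ Φ(difference/2.58 − 1.96).

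Results:

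- r = 0.1: 2 × 0.798 × 0.1 × 20 = 3.2 mm Hg; about 24%.
- r = 0.2: 2 × 0.798 × 0.2 × 20 = 6.4 mm Hg; Φ(6.4/2.58 − 1.96) ≈ 0.70.

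The split matters little. At r = 0.2, a 60/40 split gives 6.4 mm Hg (about 69%) and an 80/20 split gives 7.0 mm Hg (about 58%).

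A simulation with a 60/40 split and no true effect, in which one unmeasured factor drives both dose and SBP change, shows the same pattern. With no shared factor the false-positive rate is about 5.6%. With correlations of the factor with dose and with SBP change of 0.3 and 0.2 it is 11%; at 0.3 and 0.3, 20%; at 0.4 and 0.4, 51%; at 0.5 and 0.5, 88%.

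**The case against.** The strongest reply is that the article nowhere claims effect modification or a causal dose-response. It speaks only of testing differences between subgroups, it adjusts its effect models for several confounders, and its Discussion admits that poor compliance and unknown confounders bring bias. An exploratory label and the timing of classification may sit in a fuller plan that is not shown. The reported dose is also checked against soot on the returned boxes (section 2.9). All of this is fair, and a reader should not infer that the authors have committed themselves to a causal reading. What remains is that the text fixes both variables and tests them as hypotheses at 0.05, and neither baseline adjustment nor better dose measurement makes such a contrast a test of effect modification.

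A reader might also infer that sensation is itself a product of treatment response, for example that patients whose readings fall report it more often. The documents do not support that. Sensation may first appear at doctor-assisted point-finding, before any response. For this variable the timing is simply unstated, and the one-arm problem holds either way.

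The size is open to challenge too. The correlation is an assumption with no source in the documents. If a single shared factor accounts for r = 0.2, it needs a correlation of about 0.45 with each variable (0.45 × 0.45 ≈ 0.2), which is not small. At r = 0.1 the spurious difference is below the 5 mm Hg the trial is sized to detect. The upper end of the range should not be quoted alone.

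**Conclusion.** The point holds. As specified, neither subgroup hypothesis can test effect modification, because controls have no usable value and both variables arise after group choice. Any contrast that can be computed is open to adherence and feedback bias that the listed covariates cannot remove. This conclusion rests on the text alone and needs no arithmetic.

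The range of 3.2 to 6.4 mm Hg, significant about 24% to 70% of the time, shows what modest confounding could do. It depends on the assumed correlations, the even split and the absence of adjustment, and it is not a forecast for this trial. It is worked for dose and is not an estimate for sensation.

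A reader might go further and conclude that the primary result is compromised. It is not on this ground: these are two additional analyses, and the between-group estimate and sample size do not depend on them.

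**What to change.** - State that both analyses are exploratory within-arm associations that support no conclusion on effect modification or causal dose-response.
- State when sensation is classified. Use initial point-finding if it is, or can be, recorded then on the existing case report form; the article does not say that it is.
- Take confirmatory subgroup tests from baseline variables already collected, for example baseline SBP, each tested by a group-by-subgroup interaction. Because groups are chosen by preference, these remain subject to the trial's general confounding limits.
- If a dose analysis is still wanted, a landmark analysis (sessions in months 1 to 6 against SBP change from month 6 to month 12) is at most an optional sensitivity analysis. Its limits should be stated with it: it misses any effect already reached by month 6 and does not remove adherer bias.

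The cost is mainly wording in the analysis plan, plus a data field if initial sensation is not already captured. The downside is weaker language on dose-response.
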